### Randomization

Patients are randomized centrally by the study coordinator in a 1:1 ratio by using a web-based randomization module. Participants were stratified by center. Within each stratum, random block sizes of 2, 4, and 6 were used. Due to the large sample size, age and sex are expected to be distributed equally between the groups. Therefore, no additional strata are used.

### Blinding

Patients and treating physicians are not blinded for treatment allocation (see Discussion). However, a blinded adjudication committee will assess and weigh all events (severe complications and mortality) and decide whether the pre-specified definitions of the primary and secondary endpoints are met. The adjudication committee consists of six gastroenterologists with extensive ERCP experience, a radiologist and a nephrologist. On the basis of primary source data, each member will individually evaluate a patient’s disease course. Disagreements are resolved in a plenary consensus meeting. A final analysis will only be performed after consensus has been reached on each individual endpoint for each individual patient.

### Data collection methods and follow-up

Clinical data are collected locally on standardized digital case record forms (CRFs) before ERCP, directly afterwards and in the 24 h thereafter. CRFs were created for the endoscopist, nursing staff, and treating physician on which to score the occurrence of the primary and secondary endpoints. Endoscopy and ward nurses will monitor all intravenous fluid infusion during the first 24 h after ERCP. After 24 h, the treating physician will assess the primary endpoint (abdominal pain suggestive of PEP) and blood is drawn for measurement of serum amylase and lipase. To ensure data quality, the central study coordinator will check all CRFs and contact responsible staff members in case of inconsistencies.

All patients are followed up for 180 days after randomization. Patients are contacted by telephone after 30, 90, and 180 days by a trial nurse. The validated EQ-5D, SF-36, and iMTA PCQ questionnaires for measuring quality of life and indirect non-medical costs will be sent simultaneously by (e-)mail, with a telephone reminder after a week if there is no response [23, 24, 27]. After 1 month of non-response, another telephone reminder will follow and a new questionnaire will be sent. In case of hospitalization, patients will be interviewed by a ward nurse. If patients experienced post-ERCP pancreatitis, pancreatic function will be assessed at 180 days post-randomization by fecal elastase and serum HbA1c measurements.

Unblinded, independent monitors will visit participating sites yearly for source document verification of 10% of the CRFs, including all components of the primary endpoint. If inconsistencies are encountered, all CRFs will be inspected.

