**Fig. 1 Fig1:**
[figure not shown]
SPIRIT schedule of enrolment, interventions, and assessments. *Baseline variables: age, sex, comorbidity, American Society of Anesthesiologists score, ERCP indication, PEP risk factors, use of pancreatic duct stents. ^Primary outcome: post-ERCP pancreatitis. ^#^Secondary outcomes: incidence of delayed PEP (> 24 h after ERCP), severity of PEP, other ERCP complications, hydration-related complications, length of hospital and intensive care unit stay, health-related quality of life, cost-effectiveness, and exocrine and endocrine pancreatic insufficiency

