### Outcomes

The primary outcome is the incidence of post-ERCP pancreatitis according to the Cotton criteria [19]. The criteria of (1) new onset upper abdominal pain; (2) elevation of pancreatic enzymes (amylase and/or lipase) to more than three times the institutional upper limit of normal; (3) criteria 1 and 2 are present at least 24 h after ERCP; and (4) hospitalization (or extension of planned admission) for at least 2 nights, must all be present.

The secondary endpoints (Additional file 1) are (1) incidence of delayed PEP (PEP occurring > 24 h after the procedure); (2) severity of PEP – this will be reported according to the Cotton criteria [19] and the revised Atlanta criteria [20] since the severity grading differs between the two classifications [21, 22] and both are reported in studies; (3) ERCP-related complications according to the Cotton criteria [19], namely bleeding, perforation, and infection; (4) hydration-related complications, such as pulmonary edema and congestive heart failure; (5) length of hospital and intensive care unit stay; (6) generic health-related quality of life, measured by the EQ-5D and SF-36 [23, 24]; (7) cost-effectiveness; and (8) exocrine (fecal elastase-1 < 200 μg/L) and endocrine (HbA1c > 42 mmol/L) pancreatic insufficiency.

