### Sample size calculation

A recent meta-analysis [25] reported an 8% PEP incidence in patients receiving prophylactic rectal NSAIDs. We believe periprocedural hydration is a useful addition to rectal NSAIDs if it has a similar relative risk reduction of 60% [25, 26]. This minimal clinically important difference will cause the incidence of PEP to decrease from 8% in the control group to 3.2% in the intervention group, with a 4.8% absolute risk reduction. With a two-sided significance level of 5% and a power of 80%, a total of 718 patients (359 per treatment arm) is required to demonstrate this effect. To account for drop-out and missing data, we increased the sample size by 15%. This amounts to a final number of 826 patients (413 per treatment arm).

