### Statistical methods

#### Descriptive statistics

The baseline characteristics of age, sex, comorbidity, American Society of Anesthesiologists score, ERCP indication, PEP risk factors according to ESGE [4], and the use of other prophylactics (mainly pancreatic duct stents) will be reported. Data will be presented in percentages for categorical variables. Continuous variables will be presented as mean with standard deviation (normal distribution) or median with interquartile range (skewed distribution).

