#### Additional analyses

The secondary endpoints will be compared between treatment groups by the Student’s *t* test, Wilcoxon rank sum test, Pearson’s χ^2^ test, or Fischer exact test as appropriate. We cannot rule out the possibility that pancreatic duct stents are placed. If that scenario plays out, we will perform a sensitivity analysis of the primary endpoint in two subgroups, namely patients that only received rectal NSAIDs and patients that received combination therapy with pancreatic duct stents. Furthermore, we will conduct a sensitivity log-binomial regression analysis of our primary endpoint in which we adjust for stratification by site. Finally, the costs and effects of both treatment strategies within the 6 months of follow-up will be compared. Cost-effectiveness will be expressed as costs per patient with poor outcome (severe morbidity and/or death) and costs per quality adjusted life year up to 180 days after randomization. Healthcare costs are registered on structured CRFs. Unit prices according to the handbook of the Dutch Health Council are used [28, 29]. Productivity costs are measured by iMTA PCQ and quality adjusted life years by the EQ-5D questionnaire [24, 27]. The cost-effectiveness analysis will be reported separately from the primary study manuscript.

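### Pancreatic insufficiency is to be compared between arms but is measured only in patients who had PEP, with no listed baseline test, so the comparison is biased whichever denominator is used

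*Protocol article*

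**What the plan says.** The Outcomes section of the protocol article gives the eighth secondary endpoint as "exocrine (fecal elastase-1 < 200 μg/L) and endocrine (HbA1c > 42 mmol/L) pancreatic insufficiency". These are fixed cut-offs; neither a change from baseline nor new onset is required.

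The section on data collection and follow-up restricts who is tested: "If patients experienced post-ERCP pancreatitis, pancreatic function will be assessed at 180 days post-randomization by fecal elastase and serum HbA1c measurements". All patients are followed for 180 days, but no elastase or HbA1c measurement is described for those without PEP.

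Under Additional analyses, "The secondary endpoints will be compared between treatment groups" by standard two-group tests. No exception, denominator or separate rule is given for this endpoint.

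The legend of Fig. 1 lists "Baseline variables: age, sex, comorbidity, American Society of Anesthesiologists score, ERCP indication, PEP risk factors, use of pancreatic duct stents". The Descriptive statistics section repeats essentially the same list. Comorbidity is recorded; elastase and HbA1c are not named. The Eligibility criteria let patients with chronic pancreatitis enter when the procedure involves the pancreatic duct, and diabetes is not a listed exclusion.

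**The concern.** Whether a patient is tested depends on an event after randomisation, and that event is the primary outcome, which the trial expects hydration to reduce by 60%. The tested patients in the two arms are therefore not groups formed by randomisation. Because the endpoint is a raw threshold with no listed baseline test, a tested patient who already had diabetes or exocrine insufficiency counts as a case.

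An analysis plan can choose a denominator, but it cannot undo this measurement rule. Dividing by PEP cases introduces selection. Dividing by all patients means that pre-existing disease is detected more often in the arm with more PEP. The two faults need not act in the same direction, so a reader could not tell what a reported difference, or its absence, means.

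**Working it through.** **Inputs from the protocol article**
- PEP rates (Sample size calculation): "decrease from 8% in the control group to 3.2% in the intervention group, with a 4.8% absolute risk reduction".
- Two-sided alpha 5%, power 80%, 359 per arm, raised by 15% to 413 per arm; 1:1 allocation.

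The article gives no rate of pancreatic insufficiency. Every such rate below is an assumption.

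**1. The plan's own figure.** Two proportions, pooled variance under the null, no continuity correction, mean rate p̄ = (0.08 + 0.032)/2 = 0.056:

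n = [1.96·√(2p̄(1−p̄)) + 0.84·√(p1(1−p1) + p2(1−p2))]² / (p1−p2)²

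With unrounded normal quantiles this gives 358.995, so 359 per arm and 718 in total, as stated. 718 × 1.15 = 826. The planning rates are therefore a sound base for what follows.

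**2. How many patients are tested.**
- Control: 413 × 0.08 = 33.0
- Hydration: 413 × 0.032 = 13.2
- Total: about 46 of 826 (5.6%); about 780 are never tested.
- With 359 evaluable per arm: 28.7 and 11.5.

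**3. Denominator of PEP cases only.**

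*Equal counts (assumed 3 insufficient patients per arm).* 3/33 = 9.1% against 3/13 = 23.1%, a ratio of 2.5 against hydration. Per randomised patient it is 3/413 in each arm, a ratio of 1.0.

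*Range of case mix (assumed).* Suppose hydration prevents only milder PEP, and insufficiency follows 40% of severe and 10% of milder cases. With a severe share of 20% in control:
- Control: 6.6 severe and 26.4 milder cases; (6.6 × 0.4 + 26.4 × 0.1)/33.0 = 16.0%
- Hydration: 6.6 severe and 6.6 milder cases; (6.6 × 0.4 + 6.6 × 0.1)/13.2 = 25.0%

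| Severe share of control PEP | Within PEP, control vs hydration | Ratio | Per randomised patient, control vs hydration |
|---|---|---|---|
| 10% | 13.0% vs 17.5% | 1.35 | 1.04% vs 0.56% |
| 20% | 16.0% vs 25.0% | 1.56 | 1.28% vs 0.80% |
| 30% | 19.0% vs 32.5% | 1.71 | 1.52% vs 1.04% |

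In each row hydration is better per randomised patient and looks worse among PEP cases.

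*Opposite case.* If insufficient cases fall roughly with PEP, say 3/33 against 1/13, the rates are 9% and 8% and nothing reverses.

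**4. Denominator of all patients, raw cut-offs.** Let a proportion q have insufficiency before ERCP, equal in both arms and unrelated to PEP, and let nobody develop new disease. Expected counted cases are 413 × 0.08 × q and 413 × 0.032 × q. Their ratio is 0.032/0.08 = 0.40 for every q. The chance that Fisher's test at two-sided 5% declares a difference, by exact binomial enumeration, is:

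| Assumed q | Cases counted, control vs hydration | Chance of P < 0.05 |
|---|---|---|
| 5% | 1.7 vs 0.7 | 0.4% |
| 10% | 3.3 vs 1.3 | 4% |
| 20% | 6.6 vs 2.6 | 15% |
| 30% | 9.9 vs 4.0 | 27% |
| 50% | 16.5 vs 6.6 | 49% |

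The estimate is biased at every q; the false-positive risk becomes material only at higher prevalence.

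**The case against.** **The denominator is not stated.** This stands. A reader might infer that the plan itself would report 9% against 23%, but the article nowhere divides by PEP cases. That figure follows from one reading and from an assumed three cases per arm; equal counts over unequal denominators give 2.5 by construction, and 3/33 against 3/13 has a Fisher P of 0.33. A missing denominator alone would be ordinary analysis-plan content. The point survives because the stated testing rule biases the comparison under either choice.

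**The reversal needs a particular mechanism.** This also stands. A reader might infer that a beneficial treatment would look harmful. That requires hydration to prevent mainly mild PEP, and the Background section points the other way, citing a cohort in which more peri-ERCP hydration went with less severe PEP. The direction of the within-PEP bias is therefore unknown.

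**Pre-existing disease is partly handled.** Comorbidity is recorded, definite chronic pancreatitis is excluded outside pancreatic duct interventions, and a blinded committee rules on endpoints from source data. This lowers q but does not remove the problem. The committee applies the pre-specified definitions, which do not require new onset, and undiagnosed disease is not in the comorbidity record. The absence of baseline tests rests on two lists; the body of Fig. 1 is not shown.

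**The endpoint is minor.** It is one of eight secondary endpoints, with about 46 patients tested. The primary analysis and sample size are untouched.

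**Conclusion.** The point holds in this form: an endpoint planned for comparison between arms is ascertained according to the primary outcome, by raw cut-offs and without a listed baseline test, and is biased whichever denominator is chosen. On planning rates about 33 against 13 patients are tested. Over all patients, equal pre-existing disease alone yields a relative risk of about 0.40 in favour of hydration; this assumes the planning PEP rates, equal prevalence in the arms unrelated to PEP, and no new disease. Among PEP cases the distortion can run against hydration (ratios of 1.35 to 1.71 under the assumed case mixes, 2.5 with equal counts) or be absent.

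The documents do not support saying that the plan has adopted the PEP-only comparison, or that hydration would be made to look harmful. PEP severity raises the same issue only if it is compared among PEP cases, and the article says only that it will be reported. The unit in "endocrine (HbA1c > 42 mmol/L) pancreatic insufficiency" is a clerical slip, since HbA1c is reported in mmol/mol, and has no bearing on the argument.

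This should be changed, but it affects one secondary endpoint and not the trial's main conclusion.

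**What to change.** In the analysis plan:

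1. Define the endpoint as PEP followed by new pancreatic insufficiency, with all analysed patients of each arm as denominator and patients without PEP counted as having no event.
2. Do not count patients with recorded baseline diabetes, exocrine insufficiency or chronic pancreatitis as new cases.
3. Report percentages among PEP cases as descriptive only.
4. State that undiagnosed prior disease can be detected only in PEP cases, which leaves a bias towards hydration. The result then describes PEP-associated insufficiency; make no formal between-arm test and no claim about pancreatic function overall.
5. If PEP severity is compared between arms, use moderate or severe PEP per analysed patient.
6. Correct the HbA1c unit to mmol/mol.

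This costs wording and needs no new measurements. The price is that baseline status rests on recorded comorbidity and that a between-arm test is given up. Testing every patient at baseline and at 180 days would remove the bias, but the Trial status section reports 515 patients already randomised (515/826 = 62%), and baseline tests that were not done cannot be recovered for them.

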### Statistical methods

#### Descriptive statistics

The baseline characteristics of age, sex, comorbidity, American Society of Anesthesiologists score, ERCP indication, PEP risk factors according to ESGE [4], and the use of other prophylactics (mainly pancreatic duct stents) will be reported. Data will be presented in percentages for categorical variables. Continuous variables will be presented as mean with standard deviation (normal distribution) or median with interquartile range (skewed distribution).

#### Primary analysis

The primary endpoint will be analyzed according to the intention-to-treat principle with the use of Fisher’s exact test. That is, all randomized patients will be analyzed according to their original treatment allocation, regardless of study protocol violations. The only patients excluded from the analysis will be those in whom the duodenum was not reached and the papilla was not manipulated (e.g., in case of upper gastrointestinal stenosis, aspiration risk, restless patients). Because these patients did not have an ERCP, there is no risk of PEP. Comparison of the primary endpoint will be expressed in terms of a relative risk and 95% confidence intervals. An exploratory per-protocol analysis will also be performed. Reasons for protocol violations will be described. In these analyses we will not adjust for stratification by site. A two-tailed *P* value of less than 0.05 is considered to be statistically significant.

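### The primary test is valid but unadjusted, and no stated analysis uses the recorded PEP risk factors: the average power cost is small, and the main loss is protection against chance imbalance

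*Protocol article*

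**What the plan says.** All references are to the Protocol article.

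- **Primary analysis:** "The primary endpoint will be analyzed according to the intention-to-treat principle with the use of Fisher’s exact test". The result is reported as a relative risk with a 95% confidence interval, and the section rules out adjustment for site.
- **Additional analyses:** the only model for the primary endpoint is a "sensitivity log-binomial regression analysis of our primary endpoint in which we adjust for stratification by site". The split by pancreatic duct stent use is a subgroup comparison, not a covariate adjustment.
- **Descriptive statistics** and the **Fig. 1 legend:** "PEP risk factors according to ESGE [4" are among the baseline variables, and reporting is the only use given. The same list contains pancreatic duct stent use.
- **Randomization:** stratified by centre. Age and sex are expected to balance because the trial is large. "Therefore, no additional strata are used". PEP risk is not mentioned.
- **Background:** PEP incidence is 7-10% overall and close to 15% in high-risk patients. The trial enrols a mixed moderate- to high-risk population.

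**The concern.** By the protocol's own account, risk status predicts the outcome, and the information is collected. Neither design nor analysis uses it. With about 46 expected events, a chance difference of a few percentage points in the share of high-risk patients moves the crude relative risk and its P value in either direction. The trial is open label, so an adjustment introduced only after an imbalance has appeared would look data-driven. A pre-specified one would not.

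**Working it through.** **1. The plan's own figure.** Inputs from Sample size calculation: "decrease from 8% in the control group to 3.2% in the intervention group", two-sided 5%, power 80%. With pooled variance and no continuity correction:

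n = [1.960·√(2·0.056·0.944) + 0.842·√(0.08·0.92 + 0.032·0.968)]² / 0.048² = (0.637 + 0.272)² / 0.002304 ≈ 359 per arm.

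This matches "a total of 718 patients (359 per treatment arm) is required". Then 718 × 1.15 = 825.7, i.e. 826, or 413 per arm. Expected events: 413 × 0.08 + 413 × 0.032 ≈ 46.

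**2. Power of the planned test.** Exact enumeration for Fisher gives 76.7% at 359 per arm and 83.1% at 413, with true two-sided size about 3.4-3.7%. The z-test formula gives 80.0% and 85.2%.

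**3. Assumed prognostic strength.** The documents give no high-risk share for this trial. If it is 20-30% and the high-risk rate is 15%:

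- Overall 8%, share 30%: the rest have (8 − 0.3 × 15)/0.7 = 5.0%, a risk ratio of 3.0.
- Overall 8%, share 20%: (8 − 0.2 × 15)/0.8 = 6.25%, a risk ratio of 2.4.
- Letting the overall rate run from 7% to 10% widens the ratio to 1.7-4.2.

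Ratios of 2 to 5 are therefore shown. The top of that range exceeds the Background figure: with the control average held at 8%, share 30% and ratio 5 imply 18.2% in high-risk controls, and share 20% and ratio 4 imply 20%.

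**4. Size of chance imbalance.** The SD of the between-arm difference in high-risk share is √(2q(1−q)/413), which is 2.8 points at q = 0.2 and 3.2 points at q = 0.3.

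Hand check for share 30%, ratio 3 (control risks 15% and 5%, intervention 6% and 2%). The mean imbalance in the worst 5% of trials is about 2.06 × 3.19 = 6.6 points, i.e. shares of 26.7% (control) and 33.3% (intervention).

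- Control: 0.267 × 15 + 0.733 × 5 = 7.67%.
- Intervention: 0.333 × 6 + 0.667 × 2 = 3.33%.
- The crude difference is 4.34 points instead of 4.8.

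**5. Power with and without risk stratification.** Simulation, 40,000 trials per scenario, 413 per arm, no drop-out, relative risk 0.40, shares 20-30%:

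| Test | Power, all trials |
|---|---|
| Fisher (planned) | 83% |
| Pearson, unstratified | 86-86.5% |
| Mantel-Haenszel, stratified by risk | 87-88% |

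- Pearson to Mantel-Haenszel isolates risk adjustment: about 0.4-1.5 points over ratios 2-5, and about 0.5-0.7 when high-risk controls are at 15%.
- Fisher to Pearson, about 3 points, is the conservatism of the exact test and has nothing to do with risk factors.
- In the 5% of trials most imbalanced against hydration, Pearson has about 76-83% and Mantel-Haenszel about 87%.
- In the opposite 5%, at ratios 3-5, Fisher has 89-92% and Mantel-Haenszel 86-88%.
- With no true effect, Mantel-Haenszel rejects in about 5% of trials and Fisher in about 3.7%.

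Simulation error is about √(0.86·0.14/40,000) = 0.2 points overall and √(0.8·0.2/2,000) = 0.9 points within a 5% tail.

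**6. Cross-check by another method.** Logistic likelihood-ratio tests with and without one binary factor (odds ratio 1.5-5) differ by 0.1-1.2 points at 413 per arm. For a continuous risk score the gain is 0.1 points at AUC 0.63 and 3.7 at AUC 0.81. The documents support no particular AUC.

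**The case against.** The strongest case against runs as follows.

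- **The unadjusted test is valid.** This stands. Its size is below 5%, and chance imbalance is already covered by its unconditional error rate. A reader might infer that the primary analysis is biased or wrong; nothing in the document supports that.
- **The power gain is trivial.** This largely stands. A reader might set Fisher's 83% against 87-88% and call the difference free power lost by ignoring risk factors. Most of it is the exact test's conservatism. The worst-tail figures are also only half the picture, because unadjusted tests do better than average in the opposite tail. What remains is that the stratified test's power barely depends on which imbalance occurs.
- **The usable factors are not known.** This stands as a limit. The article does not list the ESGE factors or say which are known before randomisation, and stent use is decided during ERCP.
- **A late change adds flexibility.** This stands in part. At publication 515 of 826 patients were randomised, past the interim point of 413. It argues for a strict lock, and it is a reason some would prefer the supportive role to replacing the primary test.
- **Centre, the only stratification factor, is left out.** The site-adjusted model stays in the plan. Crossing risk with 20 centres would be very sparse with about 46 events.
- **A statistical analysis plan not shown may add an adjusted analysis.** Possible. But the article itself names the primary test and the adjustment set, so this is a stated choice and not an omitted detail.

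**Conclusion.** The point holds as a weakness of efficiency and robustness. The primary Fisher test is valid, but no stated analysis protects against chance imbalance in a predictor that the protocol records and treats as prognostic.

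Risk adjustment by itself is worth about 0.4-1.5 points of power at 413 per arm, and about 0.5-0.7 if the high-risk rate is the Background's 15%. The more useful gain is stability: about 87% power under the worst 5% of imbalances, against about 76-83% for the unstratified Pearson test.

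These figures rest on an assumed high-risk share of 20-30%, risk ratios of 2-5, the planned 8% and 3.2%, a relative risk constant across risk groups, and no drop-out. The Background rates do not come from this trial's population, which excludes low-risk patients. The documents support neither a claim of invalidity nor one of a material loss of power from omitting risk factors.

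**What to change.** - Define one PEP risk category, for example average versus high risk, from recorded factors known before randomisation. Exclude anything found or decided during ERCP, and therefore stent use.
- Lock the definition before outcomes are seen by arm, and have it set by people without access to the interim results by arm.
- Pre-specify a Mantel-Haenszel relative risk with confidence interval and test, stratified by that category. Preferably make it the primary comparison and keep Fisher as sensitivity. At minimum, name it as a supportive analysis beside the site-adjusted model.

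Mantel-Haenszel keeps the relative-risk scale already promised and avoids the convergence problems that a log-binomial model can have with about 46 events. No extra patients are needed. The cost is that the category must be fixed now, while recruitment is under way, and that the baseline factors must be completely recorded.
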